#### Inclusion criteria

2.2.2

(1) Meets the International Classification of Diseases, 10th Revision (ICD-10), diagnostic criteria for CRF;(2) Moderate to severe fatigue, defined as a score of ≥4 on the PFS;(3) Diagnosed with stage I-III breast cancer in women;(4) Age between 18 and 80 years old;(5) Karnofsky Performance Status (KPS) score of ≥70;(6) Completion of breast cancer treatment (surgery, radiotherapy, chemotherapy, targeted therapy) at least 12 weeks prior, but ongoing endocrine therapy exceeding 4 weeks is allowed.

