#### Mechanism outcomes

2.4.3

To investigate the underlying mechanisms of action of TFM, this study will collect blood and fecal samples from all participants at baseline and after a 30-day treatment period. Fasting blood samples will be collected between 7:00 AM and 9:00 AM, and the levels of serum HPA axis-related hormones, including adrenocorticotropic hormone (ACTH), corticotropin-releasing hormone (CRH), and cortisol (CORT), as well as serum inflammatory markers, including interleukin-6 (IL-6) and interleukin-8 (IL-8), will be assessed using enzyme-linked immunosorbent assay (ELISA). The gut microbiota in fecal samples will be analyzed through 16S rRNA gene sequencing. Furthermore, untargeted metabolomics analyses of serum and fecal samples will be performed using liquid chromatography-mass spectrometry (LC-MS) technology. A variety of bioinformatics approaches will also be employed for in-depth analysis of the data, including but not limited to alpha and beta diversity analysis, principal component analysis (PCA), principal coordinates analysis (PCoA), non-metric multidimensional scaling (NMDS), linear discriminant analysis effect size (LEfSe), and partial least squares discriminant analysis (PLS-DA).

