### Statistical analysis

2.9

All analyses will be conducted within the intention-to-treat population, encompassing all randomized participants. For continuous variables, data adhering to a normal distribution will be expressed as mean ± standard deviation, while non-normally distributed data will be presented using the median and interquartile range. The Shapiro-Wilk test will be used to determine the normality of the data. Categorical variables will be depicted as frequencies and percentages. The planned statistical analyses will be conducted using SPSS software (version 28.0) and the R programming language (version 4.3.1). Significance testing will be bilateral, with a P-value of ≤ 0.05 denoting statistical significance.

To compare the longitudinal trajectories of changes in PFS scores from baseline between groups at successive follow-up time points, linear mixed models will be employed. Given the correlation between repeated measures within the same participant, this model will include participant-specific random effects (29). The fixed effects of the model will include group, follow-up time, and the interaction between group and follow-up time (30). Covariates will include age and baseline PFS scores. No imputation of missing data is planned, as the analysis model itself accounts for missing data and remains valid under the missing-at-random assumption.

For other continuous outcome measures, such as KPS scores, HPA axis-related hormonal factors, and inflammatory markers, comparison between groups will employ analysis of covariance adjusting for baseline values if the data are normally distributed. If not, the Mann-Whitney U test will be applied. Missing data will be addressed through the application of the last observation carried forward method.

We plan to conduct predefined subgroup analyses for the primary outcome, considering the following baseline variables: age (≤55, >55), nutritional risk (no, yes), sleep disorder (no, yes), fatigue severity (moderate, severe), body mass index (≤24, >24), KPS score (70, 80, 90, 100), cancer stage (I, II, III), cancer subtype (Luminal A, Luminal B, HER2-positive, triple-negative), and cancer treatment (surgery, radiotherapy, chemotherapy, targeted therapy, endocrine therapy). Consequently, except for the primary outcome, the interpretations of other outcomes and subgroup analyses will be treated as exploratory.

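### For KPS and the five serum markers, a normality pre-test decides whether the analysis is baseline-adjusted; one adjusted method per outcome should be fixed in advance

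*Protocol article*

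**What the plan says.** Section 2.9 (Statistical analysis) states the gate: "The Shapiro-Wilk test will be used to determine the normality of the data". For continuous outcomes other than the PFS, "such as KPS scores, HPA axis-related hormonal factors, and inflammatory markers", it then says that "comparison between groups will employ analysis of covariance adjusting for baseline values if the data are normally distributed". The alternative is one sentence: "If not, the Mann-Whitney U test will be applied". No covariate is named for that branch, nor whether the test is applied to day-30 values or to changes. It is also not said whether normality is judged on outcome values or on model residuals.

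Baseline values exist for every affected outcome. Section 2.4.3 (Mechanism outcomes) says "this study will collect blood and fecal samples from all participants at baseline and after a 30-day treatment period". KPS is an entry criterion ("Karnofsky Performance Status (KPS) score of ≥70", section 2.2.2), and section 2.9 lists its baseline values for subgroups as 70, 80, 90 and 100.

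The same section sets the test level ("Significance testing will be bilateral, with a P-value of ≤ 0.05 denoting statistical significance"), takes all randomised participants as the analysis population, fills missing values of these outcomes by last observation carried forward, and calls everything except the primary outcome exploratory.

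**The concern.** The rule is definite, so it can be judged as written, and it has three weaknesses.

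- For KPS the stated first-choice analysis is nearly empty. A score with four possible values at entry cannot look normal to a Shapiro-Wilk test at this sample size.
- For the markers, the observed data decide both the adjustment and the quantity estimated. IL-6 could be reported as a baseline-adjusted mean difference and IL-8 as an unadjusted rank comparison, and the two could not be read side by side in one mechanism panel.
- The fallback has no covariate, although baseline is measured and the plan adjusts for it on the other branch and in the primary model. ANCOVA needs approximately normal residuals, not normal outcome values. Skewed outcome values are therefore a reason to change the scale, not to drop the adjustment.

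At stake is the precision of the mechanism comparisons, which are a stated aim of the trial and have no power calculation of their own.

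**Working it through.** **1. The plan's own figure.** The only sample size stated is for the PFS. With the pilot changes 1.93 (SD 0.47) and 0.94 (SD 0.35), margin 0.5 and one-sided α 0.025, the difference beyond the margin is 0.99 − 0.5 = 0.49. An unequal-variance t-test has power 0.9892 at 27 per arm and 0.9913 at 28, and 28/0.8 = 35. The stated 35 is reproduced. No power is stated for KPS or the markers.

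**2. How often the gate closes.** By simulation:

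- KPS outcome values: Shapiro-Wilk rejected in 100% of runs for four or five levels at 28 to 70 observations. With six levels after entry, it rejected in 93% at 35 observations and 100% at 56 or more.
- Log-normal marker, 70 observations: rejection in 74% at an assumed log-SD of 0.3, 91% at 0.4, 98% at 0.5 and 100% at 0.8. At 0.2 it was 36% (28 per arm) to 42% (35 per arm).

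At a log-SD of 0.3, two markers that behaved independently would land on different branches with probability 2 × 0.74 × 0.26 = 0.38.

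**3. Power for a skewed marker.** Assumed: effect δ = 0.6 SD on the log scale, n = 35 per arm, two-sided 0.05, baseline to day-30 correlation ρ. Power ≈ Φ(δ/(S√(2/n)) − 1.96), with 0.6/√(2/35) = 2.510. S is:

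- √(1−ρ²) for log-scale ANCOVA;
- 1/√0.955 for Mann-Whitney on day-30 values (0.955 is its asymptotic relative efficiency);
- √(2(1−ρ))/√0.955 for Mann-Whitney on changes.

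Example at ρ = 0.7:

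- ANCOVA: 2.510/0.714 = 3.515, and Φ(1.555) = 94%.
- Day-30 values: 2.510 × 0.977 = 2.453, and Φ(0.493) = 69%.
- Changes: 2.453/0.775 = 3.167, and Φ(1.207) = 89%.

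Simulation with log-SD 0.8 agrees closely:

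| ρ (assumed) | log-scale ANCOVA | Mann-Whitney, day 30 | Mann-Whitney, change |
|---|---|---|---|
| 0.3 | 73% | 67% | 55% |
| 0.5 | 79% | 66% | 68% |
| 0.7 | 93% | 67% | 88% |
| 0.8 | 98% | 68% | 96% |

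**4. Power for KPS.** Here a four-level score is cut from a latent normal variable. The latent effect is set so that ANCOVA on the uncut scale has 80% power at 35 per arm.

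| latent ρ (assumed) | ANCOVA | rank ANCOVA | Mann-Whitney, follow-up | Mann-Whitney, change |
|---|---|---|---|---|
| 0.3 | 72% | 71% | 69% | 53% |
| 0.5 | 69% | 68% | 60% | 57% |
| 0.7 | 65% | 64% | 45% | 56% |
| 0.8 | 60% | 59% | 34% | 54% |

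**5. False positives.** With no effect, and Mann-Whitney taken on follow-up values, the two-step rule rejected in 4.4% to 5.8% of runs.

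**The case against.** The strongest reply is that little depends on this. The primary PFS analysis is a mixed model adjusted for baseline, every other outcome is declared exploratory, and the error rate is sound. All of that stands, and it limits the weight of the point.

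Several stronger readings are tempting, and the documents do not support them:

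- A reader might infer that all secondary and mechanism outcomes pass through the gate. The PFS total at other times and the subdomain scores fall under the mixed model for PFS scores, and the microbiota and metabolomic data have their own methods.
- A reader might infer that baseline is discarded. That is so only if day-30 values are tested; a test on changes uses baseline, though less efficiently than ANCOVA.
- A reader might take 28 per arm as the analysed number. That is the PFS requirement before inflation for dropout. With all randomised participants and last observation carried forward, up to 35 per arm are analysed.
- A reader might assume that the markers must fail the test. That depends on skew, for which the documents give no figure.
- A reader might assume that a rank test leaves no usable estimate. The plan already describes non-normal data by median and interquartile range, and nothing rules out a location-shift estimate.

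The comparator also matters. The plan mentions no log transformation, and raw-scale ANCOVA on strongly skewed markers is no better at low correlation. With the effect set to give log-scale ANCOVA 80% power in theory, raw-scale ANCOVA had 64% and 63% at ρ 0.3 and 0.5, against 72% and 66% for Mann-Whitney on day-30 values. The remedy must therefore name the scale.

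Finally, the test might be meant for residuals. The text does not exclude this, and the near-certain failure of KPS would then be less sure. The method would still be chosen by the data.

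**Conclusion.** The point holds for KPS, ACTH, CRH, cortisol, IL-6 and IL-8 only. The rule makes the stated ANCOVA for KPS a dead letter if outcome values are tested, and it leaves each marker's method to its observed skew. A baseline-adjusted analysis on a suitable scale was more powerful than Mann-Whitney on either variable at every correlation examined.

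The size is uncertain. For markers at 35 per arm and a 0.6 SD log-scale effect, the loss on day-30 values runs from about 6 points (ρ 0.3) to 30 points (ρ 0.8). On changes it runs from about 18 points (ρ 0.3) to 2 points (ρ 0.8). The correlation, effect and skew are all assumptions, so a general statement that much of the power is lost would go too far.

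The harm is lost precision and a data-chosen method in exploratory outcomes, not false positives. The change is worth making because it is free, but the trial's main conclusion does not depend on it.

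**What to change.** In section 2.9, remove the normality switch for these outcomes and name one baseline-adjusted method for each:

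- Serum markers: ANCOVA on the log scale with log baseline as covariate, reported as a ratio of geometric means with 95% confidence interval; or rank ANCOVA.
- KPS: rank ANCOVA, or a proportional-odds model with baseline KPS as covariate.
- Mann-Whitney: at most a sensitivity analysis, stating whether it is applied to follow-up values or to changes.

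Shapiro-Wilk may still guide descriptive summaries. The cost is a change of analysis wording. No new data are needed, because baseline values of all six outcomes are already planned.

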#### Drop-out criteria

2.2.4

(1) Participants have the right to voluntarily withdraw from the trial at any stage for any reason;(2) Participants who do not formally declare their withdrawal but independently cease the prescribed treatment or participation in related examinations, or cannot be contacted during the follow-up period, will be considered to have substantively withdrawn from the trial;(3) Participants who experience severe AEs that preclude continuation in the trial;(4) Participants who show poor compliance, with fewer than 12 TFM sessions;(5) Participants who use CRF treatments outside the study protocol (e.g., stimulants or corticosteroids).

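### For the five blood markers, sampled only at baseline and day 30, last observation carried forward can only copy baseline, so a missing day-30 sample is analysed as zero change

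*Protocol article*

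**What the plan says.** Section 2.9 (Statistical analysis) sets two missing-data rules. For PFS, analysed with a linear mixed model, it says: "No imputation of missing data is planned, as the analysis model itself accounts for missing data". For the remaining continuous outcomes it says: "For other continuous outcome measures, such as KPS scores, HPA axis-related hormonal factors, and inflammatory markers, comparison between groups will employ analysis of covariance", adjusted for baseline, with a Mann-Whitney U test if the data are not normal. It then adds: "Missing data will be addressed through the application of the last observation carried forward method".

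The analysis set is fixed in the same section: "All analyses will be conducted within the intention-to-treat population, encompassing all randomized participants".

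On sampling times, section 2.4.3 (Mechanism outcomes) says: "this study will collect blood and fecal samples from all participants at baseline and after a 30-day treatment period". The text mentions no draw in between.

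Section 2.9 also limits the standing of these results: "except for the primary outcome, the interpretations of other outcomes and subgroup analyses will be treated as exploratory".

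**The concern.** Last observation carried forward (LOCF) needs an earlier post-baseline value if it is to carry any information about response. The five blood markers have none. The rule therefore writes the baseline value into the day-30 field. The ANCOVA then regresses that field on the same baseline and counts the copy as an observed result.

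Two things are at stake. A real effect on a hormone or cytokine is diluted by patients entered as unchanged. And if the arms lose different fractions of samples while both arms change over the 30 days, the unequal number of zeros creates a between-group difference that does not exist.

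Both conditions for the second problem are plausible. Both arms receive standard care, and the pilot control arm improved on PFS. The trial is open-label with a waitlist control, and one drop-out criterion in section 2.2.4 can apply only to the moxibustion arm: "Participants who show poor compliance, with fewer than 12 TFM sessions". The rule is stated outright in the article, so this is not a detail left to a separate analysis plan.

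**Working it through.** **The plan's own figure.** Section 2.7 gives changes of 1.93 (SD 0.47) and 0.94 (SD 0.35), a margin of 0.5, one-sided α 0.025, power 0.99 and 20% dropout. The effect beyond the margin is 0.99 − 0.5 = 0.49. An unequal-variance t-test calculation gives 28 per arm (power 0.9913; 27 per arm gives 0.9892), and 28 / 0.8 = 35. The stated 35 per group is reproduced, and nothing below changes it.

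**How many values would be copied.** If the planned 20% is also the fraction without a day-30 sample, that is 0.2 × 35 = 7 per arm, or 14 of 70.

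**Expected estimate under the rule.** Let D be the true effect, T the change common to both arms, and d1 and d2 the missing fractions in the moxibustion (TFM) and waitlist (WC) arms, with missingness unrelated to the values. Patients without a day-30 sample contribute a change of 0, so

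expected difference = (1 − d1)(D + T) − (1 − d2)T.

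Randomization balances baseline, so baseline-adjusted ANCOVA has the same expectation.

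- Equal missingness, d1 = d2 = d: this reduces to (1 − d)D. At d = 0.2 and D = 0.70 SD, 0.8 × 0.70 = 0.56 SD, whatever T is.
- 30% versus 10% missing, D = 0.70, T = 0: 0.7 × 0.70 = 0.49 SD.
- 30% versus 10% missing, D = 0.70, T = 0.5: 0.7 × 1.20 − 0.9 × 0.5 = 0.84 − 0.45 = 0.39 SD.
- 30% versus 10% missing, D = 0: (0.7 − 0.9)T, which is −0.10 SD at T = 0.5 and −0.19 SD at T = 0.94. Swapping the arms reverses the sign.

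**Simulation.** ANCOVA with 35 per arm, two-sided 5% test, assumed baseline to day-30 correlation 0.5. Where repeated runs differed by a point, the range is shown.

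| Missing TFM / WC | D (SD) | T (SD) | Rejection, LOCF | Rejection, observed values |
|---|---|---|---|---|
| 20% / 20% | 0.70 | 0 | 79–80% | 83% |
| 20% / 20% | 0.70 | 0.5 | 74–75% | 83–84% |
| 20% / 20% | 0 | 0.94 | 5% | 5% |
| 30% / 10% | 0 | 0 | 5% | 5% |
| 30% / 10% | 0 | 0.5 | 8% | 5% |
| 30% / 10% | 0 | 0.94 | 14–15% | 5% |

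At 20% missing, LOCF loses power although it analyses 70 patients rather than 56. The Mann-Whitney fallback does not escape the problem: applied to change scores in the last scenario, it rejected 15.5% of the time.

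The values of D and T, the correlation and the 30% / 10% split are all assumptions. The article gives none of them for any marker.

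**The case against.** The strongest reply is that little depends on these analyses. They are declared exploratory, the primary PFS analysis uses no LOCF, and the sample size rests on PFS. All of that stands, and it limits the severity.

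It is also fair that the larger error rates need unfavourable inputs. The pilot of 30 patients had no dropouts. The 30% / 10% split appears nowhere in the article. The 0.94 SD shift has the same numeral as the pilot control arm's PFS decrease in points, but nothing shows that any hormone or cytokine moves that far. With 5% missing in each arm, an effect of 0.70 SD becomes only 0.67 SD (0.95 × 0.70).

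Some stronger readings are tempting but not supported:

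- **LOCF inflates false positives in general.** It does not. With equal missingness, or with no common change, type I error stays near 5%.
- **The effect always shrinks by the missing fraction.** This is exact only when missingness is equal. Otherwise bias can run in either direction.
- **Every missing patient is entered as zero change.** This holds only where baseline is present and day 30 is absent. LOCF cannot fill a missing baseline, and a patient withdrawn for poor compliance might still give a day-30 sample.
- **The same holds for Karnofsky Performance Status (KPS).** Section 2.4.2 gives no KPS assessment times. The schedule is in Figure 2, which was not available here, so baseline copying is not established for KPS.
- **The plan contradicts itself by treating PFS differently.** PFS has four post-baseline assessments and a mixed model, while the markers have one and use ANCOVA. Different methods are not a contradiction. The PFS paragraph shows only that the authors accept a missing-at-random analysis without imputation.

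**Conclusion.** The point holds for ACTH, CRH, cortisol, IL-6 and IL-8, and it should be fixed. Given the two-sample schedule, the stated rule enters every patient with a baseline but no day-30 sample as exactly unchanged. That consequence follows from sections 2.4.3 and 2.9 alone and needs no assumption.

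The size does need assumptions. If the planned 20% dropout falls equally on both arms, the harm is a 20% attenuation with a power loss of about 3 to 10 percentage points in the 0.70 SD example, and no inflation of type I error. A false difference requires both unequal missingness and a change common to both arms. The 8% and 14–15% figures show what could happen under hypothetical inputs and are not forecasts for this trial.

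The primary conclusion is not threatened. But investigating mechanisms is a stated aim, these markers carry much of it, and calling an estimate exploratory does not remove a bias built into it.

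**What to change.** In section 2.9:

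1. Delete LOCF for the five blood markers. Analyse each with baseline-adjusted ANCOVA on observed day-30 values, which is valid if missingness depends only on arm and baseline. Alternatively, use multiple imputation with arm, age, baseline marker and PFS scores in the imputation model, which also allows missingness to depend on recorded fatigue.
2. Apply the Mann-Whitney fallback to observed values too.
3. Reconcile this with the sentence placing all analyses in the full randomized set. State that the marker analysis set is randomized participants with an observed day-30 value, or all randomized participants under multiple imputation.
4. Keep baseline carried forward at most as a labelled sensitivity analysis.
5. Make the same change for KPS only if its schedule also has no intermediate assessment.

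This changes analysis wording only. It needs no extra patients, visits or assays, and the 35 per group stands. The downside is that, without imputation, the reported n per marker falls to the observed number, for example 28 per arm at 20% missing. The change should be made before the marker data are analysed.

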### Quality control and data management

2.10

Prior to initiating recruitment for the study, it will be imperative that all researchers undergo specialized training programs. These programs will be tailored to ensure the seamless conduct of the study and to solidify understanding of trial management protocols. The training will encompass various key aspects of this trial, such as trial design, inclusion and exclusion criteria, intervention methods, outcome measurement, reporting of AEs, and the documentation in case report forms. TFM operations will be conducted by female acupuncturists who have more than three years of moxibustion experience and hold a traditional Chinese medicine practitioner’s license.

For data acquisition, paper-based case report forms will be utilized to meticulously document each participant’s demographic information and assessment outcomes. All paper-based records will be securely stored in locked filing cabinets by the study investigators. The electronic data will be entered by two experienced and independent data entry personnel using a double-entry method and will be stored in a secure, encrypted study folder accessible only to the study team. Our team will be committed to upholding the confidentiality of all data, ensuring protection against any potential breaches or losses. The research ethics committee of Chengdu University of Traditional Chinese Medicine will conduct regular audits to monitor the trial’s data, oversee its execution, evaluate its progress, and ensure its adherence to established standards and protocols.

### Trial status

2.11

Recruitment for this clinical trial is expected to begin in October 2024.

## Discussion

3

This randomized controlled clinical trial aims to evaluate the clinical efficacy and safety of TFM treatment in breast cancer survivors with CRF. In addition, the study will preliminarily explore the potential mechanisms of TFM by investigating whether it can modulate changes in inflammatory markers, gut microbiota, and the fecal/blood metabolic profile. These changes may influence HPA axis-related hormone factors, ultimately leading to the alleviation of CRF.

The HPA axis, a key component of the neuroendocrine system, regulates ACTH secretion through positive feedback mechanisms during normal stress responses, which in turn promotes CORT release. This process is crucial for maintaining immune system homeostasis and metabolic balance (31). Several studies have suggested that decreased CORT levels, combined with elevated ACTH secretion due to negative feedback mechanisms, form the physiological basis of CRF (32, 33). A retrospective clinical study found that a 4-week regimen of mild moxibustion treatment could alleviate chronic fatigue syndrome by enhancing CORT levels (34). Furthermore, inflammation is considered a critical factor in HPA axis dysfunction. Research shows that tumors and their treatments can activate pro-inflammatory cytokine networks (35). These inflammatory factors may reach the brain through various pathways, impairing CORT synthesis and release, thus contributing to fatigue (36). A study involving 108 breast cancer survivors found a positive correlation between CRF and elevated levels of IL-6 and IL-8 (37), highlighting the potential inflammatory underpinnings of this condition. A randomized controlled trial demonstrated that a 4-week course of TFM treatment could alleviate knee osteoarthritis symptoms by reducing IL-6 and tumor necrosis factor levels (38). These findings support the hypothesis that TFM may alleviate CRF through modulation of the HPA axis and inflammatory pathways.

The gut microbiota is recognized as a key mediator between the gastrointestinal and central nervous systems (39), with substantial evidence supporting its role in CRF. Research indicates that patients with milder CRF tend to have a higher relative abundance of short-chain fatty acid-producing bacteria with anti-inflammatory effects, while those with more severe CRF have an increased presence of inflammation-related bacteria (40). Moreover, an imbalance in gut microbiota can impair tight junction proteins, leading to increased gut permeability, systemic inflammation, and a weakened blood-brain barrier (41). This cascade can provoke central inflammatory responses that may worsen fatigue. Notably, a clinical trial demonstrated that a 4-week course of governor vessel moxibustion therapy may improve the symptoms of ankylosing spondylitis by increasing the abundance of *Lactobacillus*, a beneficial bacterium with anti-inflammatory properties (42). Metabolomics has been instrumental in identifying biomarkers that capture the body’s metabolic status and reactions to physiological shifts. Given that the gut microbiota serves as a major source of human metabolites, changes in its composition can profoundly affect metabolic signaling (43). Importantly, research shows that serum metabolite profiles differ significantly between CRF patients and those without fatigue, underscoring the influence of metabolic dysfunction in CRF (44). An animal study suggested that moxibustion exerts anti-fatigue effects, potentially through modulation of the gut microbiota and metabolic pathways, with increased levels of *Bacteroides* and decreased concentrations of lithocholic acid identified as key targets (45). These findings collectively support the hypothesis that TFM may alleviate CRF through its modulatory effects on both gut microbiota composition and metabolic pathways.

The use of multiple acupoints in combination may enhance therapeutic efficacy. In clinical practice, acupoint stimulation for CRF typically involves the simultaneous application of several acupoints to achieve a synergistic effect and more comprehensive therapeutic outcomes. In this study, CV6 (Qihai), CV4 (Guanyuan), SP6 (Sanyinjiao), and bilateral ST36 (Zusanli) were selected as the primary treatment acupoints. This selection is based on a data mining study on acupoint stimulation for CRF (46), which revealed that these acupoints form a core combination for effective CRF treatment. According to traditional Chinese medicine theory, the pathogenesis of CRF is often associated with Qi deficiency (insufficient vital energy). These four acupoints are known for their ability to tonify Qi and replenish deficiency, thereby helping to regulate Qi and blood and enhance the body’s restorative capacity (46). Nevertheless, further research is necessary to compare the effects of single versus multiple acupoint treatments for CRF. Such studies would provide valuable insights into optimizing acupoint selection, ultimately guiding clinical practice.

This study adopts a multidisciplinary approach to thoroughly investigate how TFM modulates biological systems associated with CRF, aiming to build a robust evidence base. However, several limitations must be acknowledged. First, as a single-center trial, the findings require validation in larger, more diverse populations. Second, challenges related to blinding and placebo effects, common in moxibustion studies, may introduce bias. Future studies should focus on developing a placebo tool specific to TFM and conducting double-blind trials to more accurately assess its efficacy. Lastly, the study does not examine certain CRF-related biomarkers, such as serotonin, which may be crucial for fully understanding the biological changes involved in CRF.

